## 10.7 Reporting of Technical Complaints about the Investigational Drug

### 10.7.1 Definitions

**Drug Technical Complaint:** A quality complaint received in writing, electronically, or orally that involves the use or attempted use of a drug product that identified any defects in the physical properties of the drug product (color, precipitates, viscosity, etc.) or its packaging. Drug technical complaints also include any identified customer dissatisfaction with the physical characteristic(s) of the drug product (dispensing characteristics, labeling, packaging, etc.).

### 10.7.2 Reporting of Technical Complaints

Any technical complaint should be reported by fax to the Sponsor's Quality Assurance Complaint Coordinator (contact information below) within 24 hours. The complaint report should include the following information:

- Name of the drug.
- Strength of drug.
- Batch/lot number on the drug container.
- Investigator name, study center name, and contact number.
- Date the complaint occurred.
- Brief description of the complaint.

- Subject involved (yes or no); if yes, were any AEs associated with the complaint (yes or no). (If a subject AE is associated with the complaint, refer to [Section 10.](#))

The drug container which initiated the complaint should be returned to the Quality Assurance Complaint Coordinator (address below) for analysis.

QLT Inc.  
Attn: Quality Assurance Complaint Coordinator  
[name]  
Vancouver, B.C.  
Canada  
[name]  
< contact information redacted >

Any complaint about a drug product or device must be reported regardless of whether the defect or deficiency had any effect on a subject or on study personnel.

## **11 STATISTICAL CONSIDERATIONS**

### **11.1 Sample Size**

The sample size of 28 subjects with LCA or RP caused by *RPE65* or *LRAT* mutation (up to 14 subjects for each disease cohort) will result in 7 subjects per genotype subgroup per disease cohort. This number is based on the small population of these LCA and RP genotypes and on clinical judgment that this is a sufficient number of subjects to meet the objectives of the study.

### **11.2 Data Sets to be Analyzed**

#### **11.2.1 Efficacy: Intent to Treat**

The intent-to-treat (ITT) data set will include data from all enrolled subjects. All data will be included and no subjects will be excluded because of protocol violations.

#### **11.2.2 Safety**

The safety data set will include data from all enrolled subjects who receive any treatment. In the safety analysis, no data exclusion is allowed because of protocol violations.

### **11.3 Analysis of Demographic and Baseline Data**

The demographic and baseline analyses will be done for the ITT data set.

Subject demographic and baseline characteristics will be summarized by gene mutation subgroup and disease cohort with mean, standard deviation, median, minimum, and maximum for continuous variables; and by counts and percentages for categorical variables.

## 11.4 Efficacy Variables and Analyses

Efficacy analyses will be performed on data from both eyes of all subjects included in the ITT data set. Each eye will be evaluated separately.

### 11.4.1 Best-Corrected Visual Acuity Using ETDRS Testing

Visual acuity scores based on ETDRS testing and changes from baseline will be provided for each time point by gene mutation subgroup and disease cohort using descriptive statistics (mean, standard deviation, minimum, median, and maximum).

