| 
Study Population:
The study plans to enroll up to 28 subjects with LCA or RP due to RPE65 deficiency or LRAT deficiency. Subjects with LCA must be 5-65 years of age (inclusive), and subjects with RP must be 18-65 years of age (inclusive) except in the US, where subjects with RP may be 8-65 years of age (inclusive). All subjects must have a best-corrected ETDRS visual acuity of 3 letters or better (20/800 Snellen equivalent). Subjects who have a lower ETDRS score are still eligible if spectral domain optical coherence tomography (OCT) and fundus autofluorescence (FAF) reveal evidence of a viable photoreceptor layer.
                                                                                                                                                                                                                                                                                                                                                                                                                                                                                                                                                                                                                                                                                                                                                                                                                                                                                                                                                                                                                                                                                                                                                                                                                                                                      |

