### 5.2 Inclusion Criteria

To be eligible for the study, subjects must fulfill all of the following criteria:

1. Subjects will have either LCA or RP, with a mutation in either *RPE65* or *LRAT*, as follows:
  - a. Subjects with LCA will be 5-65 years of age diagnosed with LCA by an ocular geneticist or pediatric ophthalmologist.
  - b. Subjects with RP will be diagnosed with RP by an ocular geneticist or ophthalmologist and be:  
For Canada, Germany, The Netherlands, and UK: 18-65 years of age (inclusive).  
For US only: 8-65 years of age (inclusive).
2. Subjects who have a best-corrected standard ETDRS visual acuity of **3 letters** or better (**20/800 Snellen equivalent**), however; subjects with a lower ETDRS score will be eligible if spectral domain OCT and FAF reveals evidence of a viable photoreceptor layer.
3. Subjects who are girls or women of child-bearing potential must not be pregnant or lactating, must have negative serum pregnancy tests ( $\geq 25$  mIU/mL sensitivity) at Screening (i.e.,  $\geq 19$  days before Day -1, and on Day -1) and must have been practicing 2 adequate methods of birth control or complete abstinence for at least 2 months.

Adequate methods of birth control include (1) use of oral contraceptives (excluding low-dose oral formulation), implantable or injectable contraceptives, or an intrauterine device (IUD), with an additional barrier method (diaphragm with spermicidal gel OR condoms with spermicide); (2) a double-barrier method (diaphragm with spermicidal gel AND condoms with spermicide); (3) partner vasectomy; and (4) total abstinence.

4. Subjects who are boys or men must (1) agree to completely abstain from sexual intercourse, (2) have had a vasectomy, or (3) use a barrier method (condoms) with spermicide during sexual intercourse, during the treatment phase of the study and for 2 months after finishing the study drug.
5. Subjects who provide informed consent and, if applicable, assent for the study (applies to subjects 7 years and older). The parent or guardian must sign an approved informed consent form for the study for subjects younger than the age of majority.

Note that use of the term "subject" throughout this protocol may also include the parent/guardian of subjects younger than the age of majority, as appropriate.

6. Subjects who are willing to comply with the protocol.

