#### 9.5.1 Best-Corrected Visual Acuity: ETDRS Testing

Best-corrected visual acuity will be measured using ETDRS testing at the visits indicated in [Table 3](#). Test distance and lighting conditions will be constant for each test. Each eye will be evaluated independently, followed by a binocular BCVA test.

See the RET IRD 01 Procedure Manual for complete instructions for BCVA using ETDRS testing.

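### Subjects below 3 ETDRS letters are admitted with no lower limit, but the only stated acuity variable is a letter score that cannot record loss from 0 or change wholly below the chart

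*Protocol*

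**What the plan says.** Criterion 2 in Section 5.2 sets entry at 3 letters or better, given as "20/800 Snellen equivalent", and then makes an exception: "subjects with a lower ETDRS score will be eligible if spectral domain OCT and FAF reveals evidence of a viable photoreceptor layer". The Protocol Summary repeats it: "Subjects who have a lower ETDRS score are still eligible". Neither place sets a lower limit or says which eye must meet the criterion.

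Section 9.5.1 names one acuity instrument: "Best-corrected visual acuity will be measured using ETDRS testing at the visits indicated in" Table 3. It adds "Test distance and lighting conditions will be constant for each test" and leaves the detail elsewhere: "See the RET IRD 01 Procedure Manual for complete instructions for BCVA using ETDRS testing".

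Section 11.4 states: "Efficacy analyses will be performed on data from both eyes of all subjects included in the ITT data set", with each eye evaluated separately. For acuity, Section 11.4.1 says: "Visual acuity scores based on ETDRS testing and changes from baseline will be provided for each time point", using mean, standard deviation, minimum, median and maximum. Section 11.5 lists the BCVA score among the safety variables and refers back to Section 9.5 for it. The protocol names no off-chart level of vision, no value to assign to an eye that reads no letters, and no count of eyes moving onto or off the chart.

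**The concern.** The exception deliberately admits eyes at or near the bottom of the scale on which acuity is then judged. Section 4.2 explains that there is no control group and that each subject's baseline serves as the control. If that baseline is 0 letters, the acuity comparison cannot show deterioration at all, and it shows improvement only once the eye reaches the chart.

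Two uses of the data are affected. Section 4.2.1 hopes the battery of tests will point to a primary endpoint for later trials, and zeros produced by the scale could make BCVA look less responsive than it is. For safety, an unchanged letter score in an eye that started at 0 gives no information about loss of acuity.

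**Working it through.** **Inputs from the protocol.** Entry below 3 letters with no lower limit (Section 5.2); ETDRS as the only acuity test named (9.5.1); letter score and change from baseline as the acuity summary (11.4.1) and the same score for safety (11.5); both eyes of every ITT subject (11.4); up to 28 subjects in two diseases and two genotypes (11.1).

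**Assumption.** The score is a count of letters read, so it stops at 0. The protocol does not state this.

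**Cell size.** 28 / (2 × 2) = 7 subjects, which reproduces the figure in Section 11.1. A cell therefore holds 14 eyes, or 7 if right and left eyes are tabulated apart.

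**Largest recordable loss.** This equals the baseline score: 0 letters from a baseline of 0, 1 from 1, 2 from 2, and 3 at the nominal entry limit. A 5-letter loss cannot be recorded in any of these eyes.

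**Recorded against true change.** Express acuity below the chart as negative letter equivalents. This is only a device; the protocol has no such scale. Then

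recorded change = max(start + true change, 0) − max(start, 0).

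| Start | True −15 | True −10 | True +10 | True +15 |
|---|---|---|---|---|
| −15 | 0 | 0 | 0 | 0 |
| −5 | 0 | 0 | 5 | 10 |
| 0 | 0 | 0 | 10 | 15 |
| 2 | −2 | −2 | 10 | 15 |

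The table separates three cases. Movement wholly below the chart is lost (first row). A gain from below onto the chart is recorded but understated: from −5, a gain of 15 is recorded as 10. From 0 or 2 letters the gains are recorded in full, and only loss is cut off.

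**Effect on a cell mean, illustration only.** Suppose every eye truly changes by 10 letter equivalents, eyes are tabulated 7 to a cell, and k of them stay below the chart at both visits. The reported mean is 10 × (7 − k)/7:

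- k = 1: 8.6 (shrinkage 1/7 = 14%)
- k = 2: 7.1 (2/7 = 29%)
- k = 3: 5.7 (3/7 = 43%)
- k = 4: 4.3 (4/7 = 57%)

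If all 14 eyes of the cell are pooled, k = 1 to 3 gives 1/14 = 7% to 3/14 = 21%. The protocol gives no basis for any value of k.

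**The case against.** The strongest reply is that the gap may be closed in documents not seen here. Section 9.5.1 sends the full testing instructions to the Procedure Manual, and recording counting fingers or light perception when no letters are read is ordinary test procedure. Nothing in the protocol forbids it. This stands as an uncertainty about what is collected. It does not change what is reported, because Sections 11.4.1 and 11.5 provide only for the letter score.

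A second reply is that BCVA is one of several measures and no success threshold rests on its mean. ERG, visual field, pupillometry, nystagmus testing, OCT, FAF and a questionnaire are also collected, and the median, minimum and maximum are reported beside the mean. For safety, worsening of an existing condition is an adverse event (10.1.1), subjects are asked about problems at each evaluation (Section 10), and fundus examination is repeated. All of this stands and limits the point to the acuity variable. These routes have their own limits: Section 4.2.1 says most of these patients have almost no measurable ERG, visual fields depend on the investigator's judgement of capability (9.5.3), and pupillometry depends on equipment (9.6.2).

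Third, a reader might infer that the chart has no usable range in the subjects admitted by the exception. That goes too far. Eyes at 0 to 2 letters keep the full upward range, and improvement is the first objective.

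**Conclusion.** The point holds for the acuity variable. The entry exception and the letter-score summaries do not fit together: followed as written, loss from 0 and any change wholly below the chart read as no change, and loss from 1 or 2 letters is capped at the baseline score. This rests on a letter count that stops at 0 and on the Procedure Manual and analysis plan not adding an off-chart variable to the reported results.

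The effect on subgroup means is unknown because the number of such eyes is not given. Three stronger conclusions might be drawn, and the protocol supports none of them:

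- **That cell means shrink by 14% to 43%.** The count of eyes is assumed, those eyes must gain as much as the rest yet stay off the chart, and off-chart gains have no agreed value in letters.
- **That such eyes are typical of LCA.** Section 1.3.1 calls LCA the most severe of these diseases but gives no acuity distribution, and Section 4.2.1 notes that many LCA and RP patients can still see, some of them quite well.
- **That loss of vision in these eyes would go unnoticed.** Adverse event reporting and the repeated eye examinations can still reveal it.

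**What to change.** At every scheduled BCVA visit, including baseline, record an off-chart category for any eye that reads 0 letters: counting fingers, hand motion, light perception or no light perception. If the Procedure Manual data or source notes already hold this, use them and cross-refer from Section 9.5.1.

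In Sections 11.4.1 and 11.5:

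- List these eyes by subject in a shift table, with the category at baseline against each visit and 'on chart' as the top category. This also shows an eye at 1 or 2 letters that later falls off the chart.
- Report letter-score change twice: for all eyes, and for eyes with at least 1 letter at baseline.

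The cost is one CRF field, about a minute per affected eye within the existing test, and one table. No eligibility or treatment rule changes. The categories are coarse and cannot be averaged with letters. Section 8.3 reports 14 subjects already treated, of up to 28 planned, so baseline categories may be missing for up to half the sample unless source notes supply them. The table should show those as missing.

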### 11.4.2 ERG Variables

Analysis of the ERG will include variables of peak time and amplitude. The a-wave amplitude will be measured from baseline to trough and b-wave amplitude will be measured from a-wave trough to b-wave peak. Peak times will be measured from the flash onset to the peak of the wave under evaluation.

The responses of both eyes for each stimulus condition will be evaluated separately, and a- and b-wave amplitudes and implicit times will be measured in photopic and scotopic conditions to estimate the cone and rod contributions, respectively. B-wave amplitudes will then be plotted against the corresponding flash intensity in order to generate the photopic and scotopic luminance-response functions from which the rod and cone  $V_{\max}$ , retinal sensitivity ( $\log K$ ) and  $ka$  and  $kd$  (for the *Photopic Hill*) parameters can be calculated according to previously reported methods.

ERG variables and changes from baseline will be summarized by gene mutation subgroup and disease cohort using descriptive statistics (mean, standard deviation, minimum, median, and maximum). In addition, the a-wave and b-wave amplitudes will be presented graphically for each group by flash intensity.

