| 
Study Design:
This will be an open-label, proof-of-concept, Phase 1b study. The study will include up to 28 subjects with LCA or RP due to inherited deficiency of RPE65 or LRAT (up to 14 subjects for each disease cohort). Subjects in each cohort (including 2 gene mutation subgroups) will receive a once-daily oral loading dose of QLT091001 (40 mg/m^2) for 7 days. This was the highest dose administered in Study RET HV 01. Subjects with either LCA or RP will be enrolled in 1 study center in Canada, a maximum of 5 subjects with RP will be enrolled at approximately 2-3 study centers in the United States, and adult subjects with RP will be enrolled at approximately 3 study centers in the European Union.
 
Subjects will be treated on an outpatient basis but will receive study treatment in the research clinic under medical supervision for each day of treatment. During the study treatment period and for 7 days post-treatment, subjects will be required to limit vigorous physical activity and will be instructed to follow dietary guidelines to avoid excessive vitamin A intake to reduce the influence of such factors on the assessment of safety variables in this study.
 
Each subject will have both eyes evaluated. Follow-up visits will continue through 12 months post-treatment, although subjects will complete the study at the Day 30 visit, or at any visit after that, if they meet entry criteria and are enrolled into a subsequent study for retreatment.
 
To determine proof-of-concept, subjects will undergo visual function testing on both eyes, including: best-corrected visual acuity (BCVA) using Early Treatment Diabetic Retinopathy Study (ETDRS) testing (monocular and binocular tests); color vision testing; visual field testing; and full-field electroretinogram (ERG) to measure cone and rod a- and b-wave amplitudes.
 |

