### **4.2.1 Rationale for Selection of Vision/Efficacy Tests**

No single test has been validated to definitively evaluate the response of treatment for LCA or RP. One potential benefit of the vision tests selected for this study will be identification of a primary endpoint for subsequent trials, if a beneficial treatment effect is observed.

While ERG testing is the gold standard for evaluating therapeutic levels of several experimental therapies and is used routinely to diagnose and monitor progression of most inherited retinal diseases including LCA, ERG testing has not yet been correlated with endpoints accepted by regulatory agencies, such as ETDRS vision and Humphrey Visual Field Analyzer (HFA). A limitation of full-field ERG is that the recording is a massed potential from the whole retina. Unless 20% or more of the retina is affected with a diseased

state, ERG recordings are usually normal (e.g., a legally blind person with macular degeneration, enlarged blind spot or other central scotomas has normal global ERGs). Most LCA and RP subjects have virtually no measurable ERG recordings, yet many of these subjects can still see, some quite well. Recent gene therapy trials for LCA have not reported changes in full-field ERG results because the methods in these trials treated less than 10% of the retina, so the ERG results would not be expected to change.

A method for quantitative analysis of Goldmann visual field (GVF) is being developed and has shown promise as an endpoint in subjects with LCA and RP in the current study, as described in the IB. (GVF has been used instead of HFA because HFA is usually not appropriate for young subjects and subjects with very low vision.) This GVF analysis is incorporated into the study for assessment as a potential primary endpoint for future trials (see [Section 11.4](#)).

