| Biomicroscopy                                                                                  | X             |                |                |                |                |                |   |   |                | X                | X                  | X                    | X                                             |
| IOP and dilated fundus exam                                                                    | X             |                |                |                |                |                |   |   |                | X                | X                  | X                    | X                                             |
| Cycloplegic refraction                                                                         | X             |                |                |                |                |                |   |   |                | X p   | X p     | X p       | X p                                |
| Full-field ERG                                                                                 | X             | X              |                |                |                |                |   |   |                | X p   | X p     | X                    | X p                                |
| Dynamic pupillometry and nystagmus testing q                                        |               | X              |                |                |                |                |   |   |                | X                | X                  | X                    | X p                                |
| Subject questionnaire (selected questions from CVFQ or LLQ; see Section 9.7. ) | X             |                |                |                |                |                |   |   |                |                  | X                  | X                    | X                                             |
| PK Sample                                                                                      |               | X              | X m | X i | X m | X i |   |   | X m | X i   |                    |                      |                                               |

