- e OCT Spectralis and FAF will be done at Month 2 and thereafter at the discretion of the Investigator.
- f Only if genetic testing to confirm the *LRAT* or *RPE65* mutation was not previously done by a fully accredited genotyping laboratory.
- g For women and girls of child-bearing potential, consent and Screening serum pregnancy test must be performed  $\geq 19$  days before Day -1. A serum pregnancy test will also be done on Day -1. A urine pregnancy test will be done on Day 14/15, Day 30, and Month 2. See [Section 9.4.1](#) for further details.
- h Month 2 only.
- i Blood samples collected predose on treatment days after a 12-hour overnight fast.
- j Only if clinically significant laboratory results were observed at the previous visit.
- k Includes heart rate, resting blood pressure, respiratory rate, and temperature and collected after a 3-minute resting period. Vital signs will be recorded predose and 4 hours postdose on treatment days.
- l Perform triplicate ECG recordings (3 readings in succession approximately 1 minute apart).
- m 4 hours postdose.
- n Two baseline BCVA tests will be done on separate days (Day -2, Day -1 and/or on Day 0 before treatment is given).
- o Color vision test can be done on Day -2/-1 or on Day 0 before treatment is given.
- p At the Investigator's discretion.
- q Dynamic pupillometry and nystagmus testing if appropriate instrument(s) is available.
- r Pre-dose measurement for BSA calculation for study drug dose.
- s At the last visit only: height only, measured for subjects  $\leq 19$  years of age only.
- t Dose must be calculated and study treatment prepared (see [Section 7.2](#)), before study treatment is administered.

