## 9.3 Treatment and Follow-up Procedures

Treatment and follow-up procedures will be done as identified in [Table 3](#).

On Day 0, each subject will receive the first dose of study drug. Treatment will be administered for 7 consecutive days (Day 0 to Day 6, inclusive).

Subjects will have follow-up visits on Days 7/8, 14/15 and 30; and Months 2, 4, 6, 8, 10, and 12. All visual function and safety assessments will be done on Day 7/8 (24/48 hours after taking the last dose of study drug). Visual function tests and safety assessments will be done on Day 14/15 and each subsequent visit. Women and girls of child-bearing potential will have urine pregnancy tests on Day 14/15, Day 30, and Month 2. AEs and concomitant medications will be monitored at every visit. The subject questionnaire will be completed on Day 14/15 and every subsequent visit. These procedures are described further in [Sections 9.4, 9.5, 9.6, and 9.7](#).

All efforts will be made for subjects to comply with the follow-up visit schedule. However, if the schedule is not feasible for a subject, follow-up visits will be conducted as closely to the schedule as possible.

Subjects will complete the study at the Day 30 visit, or any subsequent visit, if they meet entry criteria and are enrolled into a subsequent retreatment study (see [Section 1](#)).

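### Table 3 leaves full-field ERG to the investigator at 8 of 9 post-treatment visits although Section 9.3 says visual function tests will be done there, so ERG changes at those visits may describe a selected subset

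*Protocol*

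**What the plan says.** The Protocol Summary (Study Design) names the visual function tests used to judge proof of concept. The list includes "full-field electroretinogram (ERG) to measure cone and rod a- and b-wave amplitudes".

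Section 9.3, and the Post-treatment paragraph of the Summary, set the timing: "All visual function and safety assessments will be done on Day 7/8". For the later visits: "Visual function tests and safety assessments will be done on Day 14/15 and each subsequent visit".

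Table 3 has a row for "Full-field ERG". It is marked without condition at Screening, Day -2/-1 and Day 30. At Day 7/8, Day 14/15 and the Month 2 to 12 column it carries footnote p, which reads "At the Investigator's discretion". In the same table BCVA, color vision and visual field testing have no footnote p at any visit.

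Section 6 says that the study is neither randomized nor masked. Section 3 makes the duration of any improvement an objective, and Section 4.2 says that onset and duration are both still unclear. On analysis, Section 11.4.2 says that "ERG variables and changes from baseline will be summarized by gene mutation subgroup and disease cohort using descriptive statistics". The variables include amplitudes, peak times and the fitted parameters Vmax, log K, ka and kd. Section 4.2.1 says of the disease population: "Most LCA and RP subjects have virtually no measurable ERG recordings".

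**The concern.** Text and table give different instructions on whether an ERG is required at almost every visit after treatment. A site following Section 9.3 would test everyone, and a site following footnote p could test whom it likes. With centers in Canada, the US and the EU, practice may differ between them.

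The person who decides knows that the subject was treated and can see or hear how the subject is doing. If that influences who has an ERG, the mean change at a discretionary visit is that of a chosen subset, while the table labels it as a cohort or genotype result. The visits affected are the ones that speak to the end-of-treatment effect (Day 7/8) and to duration (Day 14/15 and Months 2 to 12).

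There is a smaller, related point. A change in peak time or in a fitted parameter needs a recordable waveform at both visits. If most subjects have almost no measurable ERG, those summaries may rest on very few eyes, and Section 11.4.2 does not provide for showing how many.

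**Working it through.** **1. The plan's own figure.** Section 11.1 gives 28 subjects and 7 per genotype per disease cohort: 28 / (2 × 2) = 7. This reproduces. There is no power calculation to check.

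**2. Text against table.**

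| Visit | Section 9.3 and Summary | Table 3, ERG row |
|---|---|---|
| Screening, Day -2/-1 | before treatment | required |
| Day 7/8 | will be done | discretionary (p) |
| Day 14/15 | will be done | discretionary (p) |
| Day 30 | will be done | required |
| Months 2, 4, 6, 8, 10, 12 | will be done | discretionary (p) |

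Post-treatment visits: 3 + 6 = 9. Discretionary: 2 + 6 = 8. Required: 1. The last dose is on Day 6, so the one firm ERG comes 30 − 6 = 24 days after treatment (20 to 28 days with the ±4-day window).

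**3. How far selection could move a mean.** The protocol gives no input for this, so it is an illustration. Assume a true mean change of 0 and an SD of 1. The k of n subjects ranked highest on some impression are tested, and that impression has correlation r with the ERG change. The expected shift is r × m, where m is the mean of the top k of n standard normal values (by simulation).

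| Tested | m (r = 1) | r = 0.3 | r = 0.5 |
|---|---|---|---|
| 4 of 7 | 0.62 | 0.19 | 0.31 |
| 5 of 7 | 0.42 | 0.13 | 0.21 |
| 7 of 14 | 0.75 | 0.23 | 0.38 |
| 14 of 28 | 0.78 | 0.23 | 0.39 |
| all tested | 0 | 0 | 0 |

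If the investigator instead tests those who seem to do worst, the sign reverses. If the choice is unrelated to response (r = 0), the shift is 0. For scale, the standard error of a mean of 4 is about 1/√4 = 0.5 SD, and of a mean of 14 about 1/√14 = 0.27 SD. The shift does not shrink as n grows.

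**4. Peak time and fitted parameters.** Section 4.2.1 gives no percentage, so let u be the share of subjects with no recordable ERG at baseline, taking one observation per subject. In a cell of 7, the expected number with a defined baseline peak time is 7(1 − u). The chance of at most one is u⁷ + 7(1 − u)u⁶.

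| Assumed u | Expected of 7 | P(at most 1) |
|---|---|---|
| 0.5 | 3.5 | 6% |
| 0.7 | 2.1 | 33% |
| 0.9 | 0.7 | 85% |

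This does not apply to amplitudes. They are voltage differences, and a flat trace can be scored at zero or at the noise floor.

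**The case against.** The best defense is that Table 3 governs. Section 9.3 opens by deferring to Table 3 for the procedures, and Section 9.5.4 does so for ERG timing, so footnote p can be read as the specific rule and the sentences in 9.3 as a general description. That is a fair reading, but it only settles which text would prevail. ERG would then be discretionary at 8 of 9 visits, and Section 11.4.2 would still average it like any other visit.

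It can also be said that this is a small descriptive Phase 1b study with no designated primary endpoint, and that Section 4.2.1 already admits the limits of ERG. This lowers the stakes. It does not remove the point, because the same section says that one use of these tests is to find an endpoint for later trials.

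Four stronger readings are tempting, and the protocol does not support them:

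- A reader might infer that the ERG evidence as a whole comes from a selected subset. It does not: two baseline ERGs and the Day 30 ERG are required of everyone.
- A reader might infer that discretion inflates the effect. Nothing in the protocol says how discretion is exercised, so the direction is unknown.
- A reader might infer that eyes with a flat baseline trace drop out, responders included. Section 11.4 includes both eyes of all ITT subjects, amplitude change can be computed, and Section 11.4.2 also summarizes observed values and plots amplitudes.
- A reader might turn the statement in Section 4.2.1 into more than half of study eyes. It concerns patients in general, says virtually no measurable signal, and gives no figure for the enrolled sample.

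The scoring rule and noise limit for non-recordable traces are ordinary SAP content, so their absence here is not a fault.

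**Conclusion.** The point holds as a conflict between schedule and text with a consequence for reporting. ERG is required at 1 of 9 post-treatment visits under Table 3 and at all 9 under Section 9.3. Mean ERG changes at the other 8 visits could be biased in an unknown direction if discretion is used. The shift of about 0.2 to 0.3 SD in a cell of 7 with 4 tested rests wholly on the assumed correlation of 0.3 to 0.5 and the assumed selection rule. It is smaller than the sampling error of such a cell, and it vanishes if everyone is tested or if selection is unrelated to response.

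The end-of-treatment and duration evidence is exposed. The baseline-to-Day-30 comparison is not, as planned. The recordability point is secondary and concerns only peak time, Vmax, log K, ka and kd; its size depends on a share that the protocol does not give.

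**What to change.** 1. Reconcile footnote p in the ERG row of Table 3 with Section 9.3 and the Post-treatment paragraph of the Summary. Do this for Day 7/8, Day 14/15 and Months 2 to 12, not for Day 7/8 alone. State explicitly whether the Day 7/8 ERG is required of all subjects.
2. In Section 11.4.2, base the main ERG change summary on the visits where ERG is required of everyone: Day 30 at least, and Day 7/8 if it is made mandatory.
3. List ERGs that remain discretionary separately, with the number tested out of the number attending, instead of averaging them as cohort results.
4. Limit the change summaries for peak time, Vmax, log K, ka and kd to eyes recordable at both visits, and show n. Add a paired count of recordable versus non-recordable at baseline and Day 30, and at Day 7/8 if required. The noise limit can be set in the SAP.

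Cost: a footnote edit, a few sentences in Section 11.4.2, a separate listing and one additional table. If Day 7/8 becomes mandatory, subjects who would have skipped that ERG must have one.
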